### Monitoring

#### Data monitoring

Unexpected harms are collected during the study period through e-mail, telephone or face-to-face communication between participants and co-conductors. Unanticipated adverse events including drastic worsening of symptoms, aggressive behaviour or suicide in the writing group will be communicated by the co-conductor both to the clinicians at the psychiatric centre, and to the project group. The project group will discuss if measures need to be taken. Unexpected adverse events will be reported in trial publications.

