### RCT design

The RCT is designed as an investigator-initiated, randomised, two-arm, assessor-blinded, multi-center, waiting list-controlled superiority trial. The allocation ratio to active and control condition is 1:1. The participants (*n* = 300) will be randomised to active condition (REWRITALIZE plus standard treatment) or waiting list control condition (standard treatment) (see Randomisation below). As it is a waiting list control group, the persons randomised to the control group will be invited to participate in a creative writing group after the last assessment (within one year). To ensure high methodological quality, the trial is designed and will be reported according to the SPIRIT 2013 Statement and the modified CONSORT 2017 criteria for non-pharmacological trials [15, 17]. Data will be collected at baseline, at the end of the intervention (approximately 4.5 months after baseline) and six months after the end of the intervention (approximately 10.5 months after baseline). A flow chart of the study is provided in Fig. 2.

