### Intervention

REWRITALIZE is conceptualised as a hybrid between an art group and a group therapy intervention [16]. It is developed by an interdisciplinary group of professional authors, user experts, and researchers, and it is manualised ([name], [name], [name]: Manual for REWRITALIZE, forthcoming).

REWRITALIZE consists of 15 three-hour sessions, 14 weekly with an additional session after a one-month break to reduce the risk of adverse effects at the end of the intervention. During the sessions, the 8–10 participants are presented with literary forms that function as prompts for writing exercises. Participants write spontaneously on the presented form for 5–15 min. After each text is read out loud, the participants engage in a reflective discussion about the text. The primary conductor, a professional writer with teaching experience, secures high artistic standards. S/he is supplemented by a co-conductor with clinical expertise who participates in the group activities together with the other participants and ensures psychological safety. Together they constitute the conductor-tandem. The exercises are presented during the course of sessions to participants in an order securing adherence to group therapeutic principles.

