
#### Treatment as usual

Participants are recruited from OPUS (i.e., outreach treatment of young persons with psychosis symptoms) and F-ACT (Flexible Assertive Community Treatment). OPUS is a nationally implemented 2-year-long early intervention for people with first-episode psychosis. F-ACT is a community-based treatment model that provides flexible, multidisciplinary support to individuals with severe mental illness. OPUS and F-ACT both involve enriched and flexible assertive community treatment, psychoeducation including medication and side effects, relapse prevention and family involvement [40, 75, 109]. In OPUS, a multidisciplinary team consisting of a psychiatrist, a psychologist, a psychiatric nurse, an occupational therapist, and a social worker are assigned to each patient with a 1:12 caseload. In F-ACT, a multidisciplinary team consisting of a psychiatrist, a psychiatric nurse, and a social worker are assigned to each patient. For both OPUS and F-ACT, a primary staff member is in regular contact with the patient and responsible for coordinating the treatment elements. The treatment is individual and contingent upon patients’ needs [40, 75, 109].

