#### Safety measures

Safety measures are displayed in Table 4.

**Table 4 Tab4:** Safety measures

Outcome	Measure	Pre	Post (4.5 months)	Post (10.5 months)	Source of collection
*Safety measures*	Admissions	x		x	register
	Deaths	x		x	register
	Suicide	x		x	register

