**Assessments**						
*Baseline characteristics*						
Age	x					
Sex	x					
Employment status	x					
Highest education	x					
Diagnoses	x					
Time since diagnosis	x					
Earlier use of mental health services	x					
Prior admissions (#)	x					
Antipsychotics	x					
Suicide attempt	x					
Alcohol and drug abuse	x					
*Outcome measures*						
Personal recovery QPR	x			x	x	
Connectedness TBS	x			x	x	
Self-efficacy SEPRS	x			x	x	
Functioning WSAS	x			x	x	
Quality of life MANSA	x			x	x	
Overall mentalising MentS	x			x	x	
Alexithymia TAS	x			x	x	
*Outcome measures (subset, exploratory)*						
Cognition SCIP-D	x			x		
Social cueing, TASIT 2A	x			x		
Balancing other-perspective VISPT	x			x		
Positive and negative symptoms PANSS-6	x			x		
Functioning GAF-F	x			x		
*Safety measures*						
Admissions	x					x
Deaths						x
Suicide attempt	x					x

*QPR* Questionnaire for the process of recovery; *TBS* Thwarted belongingness scale; *SEPRS* Self-efficacy for personal recovery scale; *WSAS* Work and Social Adjustment Scale; *MANSA* Manchester Short Assessment of Quality of life; *MentS* Mentalization scale; *TAS* Toronto Alexithymia Scale; *SCIP-D* Screen for cognitive impairment in psychiatry; *TASIT 2A* The awareness of social inference test; *VISPT* Visual perspective-taking task; *PANSS-6* Positive and Negative Syndrome Scale; *GAF-F* Global Assessment of Functioning Scale

Table 5 shows the participant timeline and an overview of the data collection in agreement with the standard protocol items for randomised clinical trials, recommendations for intervention trials (SPIRIT) [17]. Data are collected and stored using REDCap, an electronic data capture tool hosted at the Capital Region of Denmark. REDCap is a secure, web-based software platform designed to support data capture for research studies [41, 42].

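### The only stated route for unexpected adverse events runs through co-conductors, whom waiting-list participants do not have during follow-up, and Tables 4 and 5 define the suicide safety outcome differently

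*Protocol article*

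**What the plan says.** **Unexpected harms.** The Data monitoring section names one route: "Unexpected harms are collected during the study period through e-mail, telephone or face-to-face communication between participants and co-conductors". For unanticipated events, among which it also counts worsening and aggression, it adds that "suicide in the writing group will be communicated by the co-conductor both to the clinicians at the psychiatric centre, and to the project group". Whether to act is then decided there, and unexpected adverse events are to appear in the trial publications.

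**Who the co-conductor is.** The Intervention section describes a "co-conductor with clinical expertise who participates in the group activities together with the other participants and ensures psychological safety". The role is part of delivering the intervention.

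**What controls receive.** RCT design states that "the persons randomised to the control group will be invited to participate in a creative writing group after the last assessment (within one year"). Until then they receive standard treatment, in which "a primary staff member is in regular contact with the patient and responsible for coordinating the treatment elements" (Treatment as usual).

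**Register safety outcomes.** Table 4 (Safety measures) lists admissions, deaths and suicide, all from registers, each marked at baseline and at 10.5 months. Its third row reads "Suicide x x register". The safety block of Table 5 lists admissions, deaths and, as its third row, "Suicide attempt x x", with follow-up in the closeout column. Table 5 marks deaths at closeout only.

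**The concern.** A harms report is informative about an add-on intervention when both arms had the same chance of having an event noticed and recorded. Here the stated route exists in one arm. Worsening of symptoms or aggression in a control participant has no stated path to the trial, while the same event in a writing-group participant does. If the publication sets the resulting counts side by side, the active arm can look more harmful because of ascertainment alone. If it gives only active-arm events, readers have no background rate against which to judge them.

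The register outcomes are the natural arm-neutral comparison, so their definition matters. A completed suicide and a suicide attempt are different events. An extraction that followed Table 4 literally would leave attempts out at follow-up.

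**Working it through.** The plan states no figure on this point, so the check is mainly textual.

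**Step 1. Does the harms route reach both arms?**

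| Question | Active arm | Waiting-list arm | Source |
|---|---|---|---|
| Co-conductor during follow-up? | Yes, present in the group | No; group offered after the last assessment | Intervention; RCT design |
| Regular clinical contact? | Yes, primary staff member | Yes, primary staff member | Treatment as usual |
| Stated route from that staff member to the trial? | None | None | Data monitoring |
| Stated route for unexpected harms? | Co-conductor | None | Data monitoring |

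The Participants section counts 15–17 control groups of 8–10 people. This does not give controls a co-conductor in time: their condition is standard treatment, and their writing group comes after the last assessment. The route is therefore one-sided for the whole comparison period.

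**Step 2. Do the safety tables agree?**

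| Outcome | Table 4 | Table 5, safety block |
|---|---|---|
| Admissions | Baseline and 10.5 months | Baseline and closeout |
| Deaths | Baseline and 10.5 months | Closeout only |
| Third outcome | *Suicide*, baseline and 10.5 months | *Suicide attempt*, baseline and closeout |

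There are three discrepancies: the name of the third outcome, the baseline mark for deaths, and the follow-up point. An enrolled participant cannot have died, by suicide or otherwise, before baseline, so the baseline marks for deaths and suicide in Table 4 cannot be literal. For the third outcome, the baseline mark makes sense only for attempts. That agrees with Table 5, and Table 1 also lists suicide attempt as a register variable at baseline.

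On timing, Table 5 puts the questionnaires at t2 and t3 and the safety data at t4, a later column. Data collection gives the second follow-up as 10.5 months after baseline, but also as 10.5 months after group start. With baseline about a month before group start, the latter is about 10.5 + 1 = 11.5 months after baseline. Assignment of interventions says controls will be offered a group within one year of randomisation. If closeout falls after controls start their group, the register comparison would include control time spent in the intervention.

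**Step 3. How large could the ascertainment effect be?** The article gives no event or capture rates, so both are assumed. Inputs: n = 150 per arm (planned size, with "The allocation ratio to active and control condition is 1:1"), the same true rate p in both arms, full capture in the active arm, and a share c captured in the control arm. The recorded rates are then p and cp. Expected counts are 150p and 150cp. The chance of a nominally significant two-sided difference at 5% is approximately

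Φ{ [p − cp − 1.96·√(2·m(1−m)/150)] / √([p(1−p) + cp(1−cp)]/150) }, with m = (p + cp)/2.

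For p = 0.10 and c = 0: m = 0.05, the pooled standard error is √(2 × 0.05 × 0.95/150) = 0.0252, and the unpooled one is √(0.10 × 0.90/150) = 0.0245. Then (0.10 − 1.96 × 0.0252)/0.0245 ≈ 2.07, and Φ(2.07) ≈ 0.98.

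| True rate p | Control share captured c | Expected counts | Chance of a spurious significant difference |
|---|---|---|---|
| 5% | 0 | 7.5 vs 0 | 0.80 |
| 5% | 0.5 | 7.5 vs 3.75 | 0.21 |
| 10% | 0 | 15 vs 0 | 0.98 |
| 10% | 0.5 | 15 vs 7.5 | 0.38 |
| 20% | 0 | 30 vs 0 | 1.00 |
| 20% | 0.5 | 30 vs 15 | 0.68 |

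The normal approximation is rough at such small counts. The table shows the order of the effect and predicts nothing about this trial. The mechanism does not touch register events.

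**The case against.** **Harms can still be compared in part.** A reader might infer that no harms can be compared between arms. The article does not support that. Admissions and deaths carry the same names in Tables 4 and 5, come from registers and are not restricted by arm. The Discussion does list unrecorded use of mental health services as a limitation, but both tables plan admissions explicitly. It would also be wrong to say that Table 4 offers little beyond deaths, since admissions is its first row. This objection stands in full and limits the point to non-register events and the suicide outcome.

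**Zero capture in controls is not stated.** This is correct: the article gives no capture rates. Reasons for drop-out are registered, everyone who has not withdrawn consent is contacted for follow-up, and deterioration can show in WSAS and MANSA in both arms, and in PANSS-6 and GAF-F in the pilot subsample. These are not adverse-event reporting, but some control events could come to light. What can be said is that no route is stated.

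**No comparison of co-conductor reports is planned.** This is also correct. The section reads as monitoring of the group so that action can be taken, and it promises reporting, not a test. A spurious excess is therefore a risk if counts are set side by side, not a stated analysis.

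**The label is probably a dropped word.** This is likely, for the reasons in the table comparison. The mismatch is not arm-specific and biases nothing in itself. It still leaves the safety endpoint ambiguous in the published plan.

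**The article is condensed.** The full protocol may contain more on harms, and the announced analysis plan may fix the register window. However, the article does state a collection method, and the method it states reaches one arm.

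**Conclusion.** The point holds in a limited form. Unexpected, non-register adverse events are ascertained by a route that only the active arm has during follow-up, so they should not be set against the control arm. The suicide safety outcome, the baseline mark for deaths and the safety time point differ between Tables 4 and 5 and need to be reconciled. Register-based admissions and deaths remain comparable, and the suicide outcome will be too once defined.

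The size of any distortion cannot be derived from the article. Under the assumed true rates of 5% to 20%, it ranges from a chance of about 0.21 of a spurious difference (5%, half of control events captured) to near certainty (20%, none captured), and then only if the arms are actually compared on these reports. The primary outcome and its power are unaffected. The point rests on the article's description being complete as to the harms route.

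**What to change.** 1. Reconcile Tables 4 and 5: one definition of the suicide outcome (the baseline mark and Table 5 both point to suicide attempt), no baseline mark for deaths, and one follow-up time point in place of 10.5 months in one table and closeout in the other.
2. State that the between-arm safety comparison uses the register events, over the same window from randomisation in both arms, ending before controls are offered the group.
3. Add one identically worded harm question to the 4.5- and 10.5-month questionnaires in both arms.
4. Report events notified by co-conductors as active-arm only, with a sentence saying that they are not a between-arm comparison.

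Items 1, 2 and 4 are changes of text, and the register extraction is already planned. Item 3 uses contacts already scheduled in both arms; its downside is one more questionnaire item. Because participants know their allocation, answers to that item may still differ by arm in willingness to report, but the opportunity to report will be equal.

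### Outside the register measures, adverse events are collected and published only if unexpected, although the protocol itself foresees adverse effects when the group ends

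*Protocol article*

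**What the plan says.** Three sentences in the Data monitoring section govern adverse events, and each carries a condition of expectedness.

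- Collection: "Unexpected harms are collected during the study period through e-mail, telephone or face-to-face communication between participants and co-conductors".
- Escalation: "Unanticipated adverse events including drastic worsening of symptoms, aggressive behaviour or suicide in the writing group will be communicated by the co-conductor", to the clinicians and to the project group.
- Publication: "Unexpected adverse events will be reported in trial publications".

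The Intervention section describes 14 weekly sessions, "with an additional session after a one-month break to reduce the risk of adverse effects at the end of the intervention".

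The Safety measures section has a separate route: "Safety measures are displayed in Table 4". That table lists admissions, deaths and suicide, all from registers, marked before the intervention and at 10.5 months. Table 5 lists admissions, deaths and suicide attempt at closeout. Neither table sets a condition of expectedness.

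**The concern.** A protocol that adds a session to reduce a risk has foreseen that risk. If its adverse-event log then takes only what was not foreseen, the log may miss the kind of event for which that session was added. The article does not simply leave the matter to a fuller document: it states a rule, and the rule is restrictive. A later analysis plan can change how recorded events are tabulated, but it cannot recover events that were never logged.

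What is at stake is the completeness of the harm report, not the primary analysis of the QPR. The Discussion says that a positive result would allow the intervention to be offered at mental health centres across Denmark. Readers weighing that step would need the foreseeable harms as well as the surprising ones.

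**Working it through.** No arithmetic decides this point. The check is to sort possible events by two features, whether they were foreseen and whether they leave a register trace, and to look for a stated route for each.

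| Event | Stated route into the harm record |
|---|---|
| Admission, death, suicide or suicide attempt, foreseen or not | Yes: Tables 4 and 5 |
| Other event, not foreseen | Yes: Data monitoring, collection and publication |
| Other event, foreseen | None stated |

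The third row is the gap. The Intervention section shows that the row may not be empty, because it names adverse effects at the end of the intervention as a risk to be reduced.

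The next question is whether other data fill the row.

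- **Symptom scale.** PANSS-6 is used only in the pilot subsample, at baseline and 4.5 months (Table 3). That leaves 300 − 70 = 230 participants, or 230/300 = 77%, without it, and nobody has it in the 10.5 − 4.5 = 6 months between the two follow-ups. These figures describe the coverage of one scale. They do not count missed harms.
- **Full-sample questionnaires.** QPR, TBS, WSAS, MANSA and the other self-report scales are collected in both arms at 4.5 and 10.5 months (Table 5), so worsening would leave a trace there. The Data analyses section compares group means, however, and a minority who worsen need not show in a mean. The questionnaires are efficacy measures and are not described as part of the harm record.
- **Service contacts.** The Discussion states as a limitation that use of mental health services is not recorded, so worsening managed without admission would not show there either.

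Finally, the timing. The collection sentence covers the whole study period, so the one-month break and the time after session 15 are not excluded by date. What excludes a foreseen event is the word unexpected, not the calendar. The phrase "Unanticipated adverse events including drastic worsening of symptoms, aggressive behaviour or suicide in the writing group" adds an ambiguity: the closing words about the writing group may limit only suicide, or all three examples, and may refer to the sessions or to the group's members.

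**The case against.** The strongest case on the other side has four parts.

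1. **Registers.** The most serious consequences are captured whatever the expectation. This stands, and it limits the point to events without a register trace.
2. **Worsening is named.** Drastic worsening of symptoms is one of the listed examples, so a deteriorating participant may well be reported in practice. Reducing a general risk also does not make one person's deterioration expected. This stands in part. The example is given as a kind of unanticipated event, so whether it applies is left to the co-conductor's judgement of what was foreseen.
3. **The foreseen effect is not described.** The Intervention section does not say what the adverse effects are, so it cannot be shown that they fall wholly outside the record. This stands. The gap concerns what the wording allows, and its content is unknown.
4. **This is a condensed article.** Definitions of adverse events are commonly left to the full protocol, and the article never says that expected events will be ignored. This carries less weight, because the restriction is stated at each of the three steps.

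Some stronger readings are tempting but unsupported. A reader might infer that only unexpected harms are collected anywhere in the trial; Tables 4 and 5 show otherwise. A reader might infer that nothing else captures worsening; the questionnaires run to 10.5 months in everyone. A reader might infer that better wording would let the trial judge whether session 15 worked; session 15 belongs to the intervention for the whole active arm, so nothing isolates its effect. Nor does prespecifying suicide as a safety outcome contradict treating a particular suicide as unanticipated.

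**Conclusion.** The point holds in a limited form. For adverse events outside the register measures, collection and publication are restricted to the unexpected, while the protocol foresees adverse effects at the end of the group. A foreseeable deterioration at that stage that leads to no admission, suicide attempt or death has no stated route into the harm record, so the published harms could be incomplete.

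The size cannot be derived: no rate of such events is given and their nature is not described. The conclusion rests on a literal reading of the word unexpected and on no unseen document overriding it. The primary analysis is unaffected.

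**What to change.** In the Data monitoring section, remove the expectedness condition from the collection and publication sentences. State that adverse events in the categories already named there are recorded and reported whether or not they were expected and whether or not they occur in a session. State also that this applies throughout the study period, including the one-month break and the time after session 15.

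Two passages need reconciling only. The escalation sentence should be brought into line with the Intervention section and Table 4, including what its words about the writing group are meant to limit. Who is informed of which event is a clinical matter for the investigators. The entry for suicide in Table 4 and for suicide attempt in Table 5 should be made to agree.

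The cost is a few sentences and somewhat more events to log. The collection route runs through the co-conductors, and no equivalent is described for waiting-list controls, so the fuller log would mainly describe the active arm and should not be read as a comparison between arms.

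A descriptive table of participants whose QPR falls by at least 4 points would be optional and is not part of this correction. Such falls are common by chance. With the protocol's SD of 10 and an assumed correlation r between baseline and follow-up, the SD of change is 10 × √(2(1 − r)): 10.0 at r = 0.5 and 6.3 at r = 0.8. With no mean change and a normal distribution, the proportion falling by 4 points or more is Φ(−4/10.0) ≈ 34% and Φ(−4/6.3) ≈ 26% respectively.
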